### Randomization

At least 172 residents will be included; 86 will start in the intervention group who follow the stepped care protocol. The other 86 will receive care as usual. Subjects are randomized at the patient level per home in computer generated blocks of four by an independent statistician, simultaneously with the inclusion in the study. Blocking is used to ensure that comparison groups are of approximately the same size per home.

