##### Step 2: biblio-therapy and a signal to the GP

Participants, who still have symptoms of depression and anxiety after 3 months of watchful waiting, as measured with the CES-D, are informed about the possibility of learning to cope with these symptoms by a self-help course for coping with depression and anxiety with an accent on activity scheduling. Self administered treatments for depression and anxiety have proven to be successful in clinical practice and for older adults [19,34-39]. Staff will be trained to accompany and stimulate the residents while working through the course in their own tempo. At the same time, GPs will be involved by informing them about the persisting symptoms. After a period of three months the third measurement will take place.

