### Blinding

Interviewers are kept blind from the randomization status of participants. It is not possible to keep the residents blinded. Staff members in the homes for the elderly and GPs are not informed about allocation of the residents. However, as residents receive questionnaires, staff will be aware of participation of the residents in the project.

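### A single fixed block size of four within each home makes up to a third of allocations, on average, foreseeable if earlier allocations in that home become known; varying, undisclosed block sizes would largely remove this certainty

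*Protocol article*

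**What the plan says.** In the protocol article, the Randomization section states: "Subjects are randomized at the patient level per home in computer generated blocks of four", and adds that this is done "by an independent statistician, simultaneously with the inclusion in the study". The target is 86 residents per arm, so each block holds two places for each arm. The stated purpose is balance by home: "Blocking is used to ensure that comparison groups are of approximately the same size per home". No second block size and no variation in size is mentioned.

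On who knows what, the Blinding section says of residents: "It is not possible to keep the residents blinded". Of the assessors it says: "Interviewers are kept blind from the randomization status of participants". The same section adds that home staff and GPs are not told the allocation. The Step 2 section, however, gives staff a part in delivering the self-help course: "Staff will be trained to accompany and stimulate the residents while working through the course in their own tempo".

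**The concern.** Independent generation of the list keeps its contents out of recruiters' hands. It does not stop someone from inferring the next place from places already filled. With one constant, small block size inside each home, anyone who knows the order of inclusion and the arms given so far can sometimes name the next arm with certainty. Residents are one possible source of that information, because they know their own arm.

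Concealment is what is at stake. The MINI and MMSE checks (Participants section) and consent to randomisation (assumed at 80% in the Sample size section) come before allocation. Foreknowledge at that stage could influence who enters. The primary outcome is a MINI diagnosis made by interviewers who are meant to be blind, so one also has to ask whether block size threatens that blinding.

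**Working it through.** The article gives no figure for predictability, so there is none to reproduce.

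**Inputs.** Block size 4, stratified by home, 1:1 allocation (Randomization section). Home size is not stated; 2 to 43 residents per home is assumed. The probability q that an earlier resident's arm is known to the observer is not stated either; 0 to 1 is shown.

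**1. Full knowledge of earlier places.** A block with two places per arm has 6 possible sequences. In 2 of them (AABB, BBAA) the last two places are certain; in the other 4 only the last is.

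- Certain places per block: (2×2 + 4×1)/6 = 8/6 = 1.33 of 4. This is 8 of 24 positions, or 33.3%.
- Best guess by position: 1/2, 2/3, 2/3, 1. The sum is 17/6, and divided by 4 it is 17/24 = 70.8%, against 50% without information.

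**2. Partial knowledge.** The third place is certain only if the first two share an arm (probability 1/3) and both are known (q²). The fourth is certain if both members of the matching pair among the first three are known (q²). The share is (q²/3 + q²)/4 = q²/3.

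| q | share certain |
|---|---|
| 0 | 0% |
| 0.25 | 2.1% |
| 0.5 | 8.3% |
| 0.75 | 18.8% |
| 1 | 33.3% |

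**3. Incomplete last block, full knowledge.** Adding 0, 0, 1/3, 1 over successive places and dividing by the number of residents in the home gives:

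| residents in home | share certain |
|---|---|
| 2 | 0% |
| 3 | 11% |
| 5 | 27% |
| 6 | 22% |
| 10 | 27% |
| 43 | 32% |

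**4. Varying block sizes.** Simulation with 16 residents per home; the observer knows the full history and the set of sizes in use.

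| scheme | certain | best guess right |
|---|---|---|
| fixed 4 | 33% | 71% |
| random 4 and 6 | about 6% | about 68% |
| random 4, 6 and 8 | about 3% | about 67% |

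**5. Interviewer blinding.** This is a retrospective question, and the one-third figure does not measure it. Suppose two residents' arms are known in a home of N residents in complete blocks, the two being a random pair. They settle anyone else's arm only if they share a block, probability 3/(N−1), and an arm, probability 1/3. The product is 1/(N−1): 9% at N = 12, 5% at N = 20, 3% at N = 40. With three known residents there are three mutually exclusive pairs, so the chance is 3/(N−1): 27%, 16% and 8%. Even then the interviewer must know which residents make up each block.

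**6. Cost in balance.** The largest imbalance within a home is half the largest block: 4/2 = 2 now, and 6/2 = 3 with sizes 4 and 6.

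**The case against.** Small permuted blocks within site, allocated by an independent statistician at inclusion, are a common and defensible choice. The article says interviewers, staff and GPs are not told the allocation; if that holds, q is near zero and so is the deducible share. Step 1 is watchful waiting, so for the first three months active treatment does not distinguish the arms. Only intervention residents with persisting symptoms reach Step 2, so not receiving the course does not identify a control. Entry rests largely on fixed instrument thresholds. The article does not show that recruiters knew the block size or earlier arms, and its appearance in print does not establish that. Finally, best-guess success hardly moves under the remedy.

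Most of this stands, and it limits the size of the point. It does not remove it, because a list generated independently can still be predicted once unblinded residents disclose their arms. The staff role in Step 2 is also hard to square with staff not knowing the allocation. Those two sections must be reconciled, but that conflict exists whatever the block size.

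A reader might go further and infer that learning two or three residents' arms in a home reveals the others, so that the fixed block undermines interviewer blinding. The documents do not support this: it requires shared blocks and known block membership. The more direct threat is a resident disclosing his or her own arm at interview, which block size does not affect. Nor does the fixed block lack any benefit. It gives the tightest balance per home of the schemes compared here, and balance is its stated purpose.

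**Conclusion.** The point holds as a minor, avoidable weakness in allocation concealment. One third is the long-run average for complete blocks and an observer who knows the order and arm of every earlier participant in the home. It is a ceiling and not an estimate of what will happen. Under partial knowledge the share is about q²/3, with q an assumption that the documents do not inform, and incomplete last blocks reduce it further. A reader should not conclude that a third of allocations will in fact be foreseen, or that selection bias has been shown. Block size adds only marginally to the risk to interviewer blinding.

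**What to change.** For homes not yet started, replace the blocks of four by permuted blocks of randomly varying size (for example 4 and 6), still stratified by home. The independent statistician alone should hold the sizes and the list; homes, recruiters and interviewers should not have them. While recruitment is open, the public description need say only that block sizes vary.

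The cost is a new computer-generated list for those homes and a largest within-home imbalance of 3 residents instead of 2, which still serves the aim of near-equal arms per home. The gain lies mainly in removing certain knowledge (33% to about 6% for a fully informed observer). Informed guessing improves only slightly (71% to about 68%).

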### Blinding

Interviewers are kept blind from the randomization status of participants. It is not possible to keep the residents blinded. Staff members in the homes for the elderly and GPs are not informed about allocation of the residents. However, as residents receive questionnaires, staff will be aware of participation of the residents in the project.

### Analysis

To examine differences on the primary outcome, survival analysis will be used. The secondary outcome measures are analysed using random coefficient analyses. The analyses will be performed according to the "intention to treat" principle. Additionally, data will be analyzed according to the per protocol principle. Differences in total costs between both groups are assessed and confidence intervals are estimated using bias-corrected and accelerated bootstrapping with 2000 replications [54]. Cost-effectiveness and cost-utility ratios will be calculated by dividing the difference in total costs between the intervention and usual care group by the difference in the clinical effect measures and QALYs between the treatment groups. Uncertainty around the cost-effectiveness and cost-utility ratios will calculated using the bias-corrected percentile bootstrapping method (5000 replications) [55]. The bootstrapped cost-effect pairs were plotted on a cost-effectiveness plane.

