### Sample size

Based on the prospective data of the Longitudinal Ageing Study Amsterdam (LASA) we conservatively estimate the incidence rate of depressive and/or anxiety disorder of elderly with symptoms of anxiety and/or depression within two years at 35% [33,52]. Our aim is to reduce incidence of full blown anxiety and depression disorders in the prevention group to 20%. To be able to detect this reduction (alpha = 0.5 and power = 0.80) 134 completers are needed, 67 in both conditions [53]. In the population of elderly persons in residential homes, substantial drop out (attrition) is expected because of illness and mortality. This is estimated at 20%, so therefore we need 172 participants. We know from previous projects that two thirds of subjects complete the CES-D, and we assume 40% will score 16 or more [22]. We estimate that 20% of these subjects already have a depressive and/or anxiety disorder and therefore will be excluded. With 80% consenting for randomization, we conservatively need to screen 1200 residents to find 86 residents per arm.

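### The bias-corrected percentile intervals planned for the cost-effectiveness and cost-utility ratios lose their meaning when bootstrap replicates cross zero effect, which is likely at this trial's size

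*Protocol article*

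**What the plan says.** The Analysis section of the protocol article defines each ratio as the between-arm difference in total costs divided by the between-arm difference in a clinical effect measure or in QALYs. On uncertainty it says: "Uncertainty around the cost-effectiveness and cost-utility ratios will calculated using the bias-corrected percentile bootstrapping method (5000 replications". It adds: "The bootstrapped cost-effect pairs were plotted on a cost-effectiveness plane". It does not say what happens to the ratio interval if replicates lie on both sides of zero effect. The cost difference on its own gets a separate bias-corrected and accelerated bootstrap interval with 2000 replications, which is not in question here.

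The Sample size section supplies the effect inputs: a two-year incidence of 35% under usual care, a target of 20% in the prevention group, and "134 completers are needed, 67 in both conditions". The Randomization section plans 86 residents per arm.

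**The concern.** A bias-corrected percentile interval orders the replicate ratios and reads off two of them. That works only if the order means something. Take a cost difference of EUR 500 and an effect difference of 0.15. Saving EUR 500 with 0.15 fewer cases per resident gives −500/0.15 = −3,333. Spending EUR 500 more with 0.15 extra cases per resident gives 500/(−0.15) = −3,333. The first is the best possible result and the second the worst, yet they share a rank. Positive ratios have the same ambiguity (dearer and better, or cheaper and worse). Near zero effect the ratio also runs off to plus or minus infinity.

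When an appreciable share of replicates crosses zero, the order no longer runs from good value to poor value. Bias correction moves the percentile points but does not restore the order. At stake is whether the trial's stated error limits on its two economic ratios can be read as a range of value for money.

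**Working it through.** **1. The plan's own figure.** For 35% versus 20% with power 0.80, the pooled two-proportion formula at two-sided alpha 0.05 gives

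n = [1.96·√(2·0.275·0.725) + 0.842·√(0.35·0.65 + 0.20·0.80)]² / 0.15² = 138 per arm.

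The protocol's 134 in total, 67 per arm, is therefore not reproduced, and the printed "alpha = 0.5 and power = 0.80" does not reproduce it either (41 per arm two-sided, 13 one-sided). With 67 per arm, two-sided power at 0.05 is about 49%. That is a separate matter. It counts here only because 67 per arm is what the plan fixes and it makes crossing more likely.

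**2. Chance that the effect crosses zero.** I assume that the clinical effect in the ratio is the difference in incidence. Under a normal approximation, more than 2.5% of replicates fall at or below zero when the 95% interval for the effect difference reaches zero. With difference d and standard error SE,

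P = Φ(1.96 − d/SE) − Φ(−1.96 − d/SE).

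- Planned effect, 67 per arm: SE = √[(0.2275 + 0.16)/67] = 0.0760; d/SE = 0.15/0.0760 = 1.97; P = 49.5%.
- Planned effect, 86 per arm: SE = √(0.3875/86) = 0.0671; d/SE = 2.23; P = 39%.
- A 30% relative reduction, the upper end of what the Background reports from other prevention studies (35% versus 24.5%), 67 per arm: SE = √[(0.2275 + 0.1850)/67] = 0.0785; d/SE = 0.105/0.0785 = 1.34; P = 73%. With 86 per arm, P = 67%.
- Planned effect, 138 per arm: P = 19%.

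The protocol gives no QALY inputs. Assuming SD 0.25, SE = 0.25·√(2/67) = 0.043, and P is 89% for a gain of 0.03 and 79% for 0.05. Over assumed SDs of 0.15–0.30 and gains of 0.01–0.05, P runs from 51% to 95%.

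**3. Coverage by simulation.** Cost inputs are assumptions: a true cost difference of EUR 500–1500 with SE EUR 600. Cost and effect differences were drawn as normal, in 2000 trials with 2000 replicates each and 67 per arm.

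| True effect | Coverage of nominal 95% ratio interval | Net-benefit interval |
|---|---|---|
| 15 points | about 91–93% | about 95% |
| 10.5 points (30% relative reduction) | about 85% | about 95% |
| QALY gain 0.03–0.05, SD 0.25 | about 66–83% | about 95% |

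A second simulation resampled individual lognormal costs (assumed mean EUR 5000 against 5000–6000, coefficient of variation 1). It gave 91–92% at the 15-point effect. For QALYs it gave 86% (gain 0.05, SD 0.20) and 70% (gain 0.02, SD 0.20).

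**4. Width.** At the 15-point effect in the first simulation, the median width was about EUR 160,000–460,000 per case averted in trials where more than 2.5% of replicates crossed zero. In the other trials it was about EUR 20,000–28,000. The true ratio at a cost difference of EUR 500 is 500/0.15 = EUR 3,333.

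**The case against.** The strongest reply is that little harm follows. For the incidence ratio, the only one whose effect inputs come from the protocol, undercoverage at the planned effect is modest. With all 86 per arm analysed, crossing drops to 39% and coverage is close to 94%, although that ignores the 20% attrition the plan itself expects. The lowest coverage figures rest on assumed costs and QALYs. The planned cost-effectiveness plane would show any scatter across quadrants, and the article condenses a fuller plan that might order replicates by quadrant.

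Much of this stands. For the incidence ratio the failure is mainly one of interpretation, and the QALY figures are illustrations rather than estimates for this trial. But the plane does not repair an interval reported beside it, and the method is stated without any condition.

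Three stronger readings are tempting and are not supported:

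- A reader might infer that the limits will be falsely tight. The widths above show the opposite: when replicates cross, the interval is typically enormous, yet it still covers below 95%.
- A reader might infer that a headline result is at risk. The Background names preventing onset of disorder as the primary aim and puts costs among the secondary aims.
- A reader might count the lack of a net-benefit analysis or acceptability curve as an error. A condensed article may leave these to the full plan, so their absence is not the finding. The finding is the interval method that the article does state.

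**Conclusion.** The point holds, as a flaw in a stated secondary analysis. Followed as written, the plan yields ratio limits that cannot be interpreted in about half of trials at the planned effect with 67 per arm, and in about 73% if the benefit is a 30% relative reduction. Those two figures need only the protocol's inputs, a normal approximation, and incidence as the effect measure. The loss of coverage is small for the incidence ratio at the planned effect and probably larger for the cost-utility ratio, but its size depends on cost and QALY inputs that the protocol does not give. The primary survival analysis and the interval for the cost difference are unaffected.

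**What to change.** In the Analysis section, replace the bias-corrected percentile interval on the ratios with intervals on incremental net monetary benefit (willingness to pay × effect difference − cost difference), over a stated range of willingness-to-pay values and from the same 5000 replicates. Report each ratio as a point estimate only, and give the share of replicates in each quadrant beside the planned plane. A lighter alternative is to report the ratio interval only when replicates do not cross zero. At the planned effect with 67 per arm, that would leave about half of trials without an interval.

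The cost is a change of wording and slightly more analysis and reporting, with no new data or participants. The drawback is that readers get no single interval on the ratio and must choose a willingness-to-pay value to read the result.

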## Discussion

By presenting the design of this study before the results are available we aim to offer researchers the opportunity to consider the methodological quality of this study with a critical view. Caregivers can benefit by considering the information on the practical applications of the proposed protocol on a vulnerable group of residents of homes for the elderly.

The importance of psychiatric disorders to public health makes prevention a serious issue. Indicated prevention has proven to be a very promising field [56]. Nevertheless, the number of studies examining the effects of preventive interventions on the incidence of mental disorders is very small, especially among elderly [14]. With this study we aim to supply more scientific knowledge to base guidelines for this kind of interventions on.

This study evaluates the effectiveness of a stepped care protocol for prevention of depression and anxiety in homes for the elderly in the Netherlands, while a similar study is conducted in the community. This offers the possibility to compare the results in these different elderly populations. This comparison may supply further information about effectiveness and feasibility of this prevention strategy in different populations of the elderly.

Another strength of the chosen prevention strategy is the focus on the combination of symptoms of depression and anxiety. Risk factors for the onset of these disorders overlap [57,58]. Focussing on the combination of symptoms of a target group with high risk, may therefore increase the effect of the intervention.

The randomization is at the patient level. The risk of confounding is merely applied to the one step in the intervention protocol where staff members, all or not provide and stimulate the self-help manuals. Therefore extra efforts will be attended to instructing the staff. Moreover, research on training and education of caregivers in primary care [59-61] shows that the influence of short courses on attitude in the management of patients with mental illness as on patient outcomes is relatively small. Therefore, contamination with the usual care group is neglectable. Finally, the main disadvantage of cluster randomisation, either on ward or on home level, is lack in unity of wards and homes.

The use of a self-help course as a second step in the protocol has numerous advantages. In the first place, it can be an efficient and high quality form of therapy [35]. Secondly, a self-help course may lower the threshold for those who don't want or dare to ask for therapist treatment. Moreover, it may contribute to the effectiveness of the following step (if necessary) by preparing the client for therapeutic treatment. On the other hand, unsuccessfully treatment may cause less willingness to undergo further, more involved treatment. Therefore, a thorough explanation of the rationale and procedures of the stepped care model is important.

Activities in this prevention program are addressed to people who are at risk to develop a serious disorder, but have no explicit request for treatment. The interventions therefore need to be non threatening and short time limited. Life review seems to be a very useful method as it is a non-stigmatising, easy to use and easily administered treatment method, suitable for elderly residents [40,62].

The results of this RCT will provide valuable information about the feasibility and (cost)effectiveness of a stepped care protocol for prevention of depression and anxiety disorders in residential homes for the elderly. Moreover, positive effects may stimulate the further development and use of guidelines by caregivers in homes for the elderly for psychiatric issues and thereby improve the quality of living in these environments. The start of the study is anticipated for October 2006 with results available in 2010.
